### Participants

2.2

Patients will be recruited from secondary hospitals throughout the Netherlands from January 2025 till December 2026.

Overweight or obese patients with persistent (≥3 months) non-specific LBP, who experience decreased physical functioning, and are referred back from hospital care to primary care, are eligible for inclusion. Patients need to be at least 18 years of age and have either a body mass index (BMI) ≥30 (i.e., obese) or a BMI ≥25 (i.e., overweight) with at least one of the following factors: osteoarthritis, sleep apnea, risk factors for cardiovascular diseases or type 2 diabetes in line with the reimbursement criteria for combined lifestyle interventions in the Netherlands [30]. Non-specific low back pain was defined according to the Dutch general practice and physiotherapy guidelines as low back pain without a clearly identifiable specific anatomical or pathological cause explaining the symptoms [11,12]. Classification into specific or non-specific low back pain was made by the recruiting medical specialist based on clinical assessment, history, physical examination, and available diagnostic information in accordance with routine clinical practice. Additionally, patients need to experience an average LBP intensity of ≥3 out of 10 on a numeric pain rating scale (NPRS) over the past week and a physical functioning score of ≥4 out of 24 on the Roland-Morris Disability Questionnaire (RMDQ).

Patients will be excluded if they are diagnosed with specific LBP (e.g., fracture, radiculopathy, tumour, or infection), have a psychiatric condition that, in the clinical judgment of the recruiting medical specialist, is considered likely to interfere with study participation (e.g., schizophrenia), are currently pregnant, or are less than nine months postpartum. No predefined diagnostic criteria or questionnaire cut-off scores were used for this exclusion criterion.

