#### Co-primary outcomes: physical functioning and physical activity

2.5.1

The co-primary outcomes are physical functioning and physical activity (i.e., average steps per day over 7 days).

Physical functioning will be measured using the RMDQ [32]. This is the most important domain in the core outcome set for LBP [33]. The RMDQ is a 24-item self-report questionnaire about how LBP affects functional activities. Each question is worth one point so scores can range from 0 (no disability) to 24 (severe disability). The RMDQ is a reliable tool to measure the impact of LBP on physical functioning [34].

Physical activity will be assessed with the activPAL activity monitor (activPAL4, PAL Technologies LTD., Glasgow, U.K.) [35]. The activPAL measures physical activity and sedentary time through measuring accelerations and posture of the thigh [36]. The activPAL is a small non-invasive electronic logging device designed to quantify free-living daily activities. Participants follow a nine-day wear protocol, where the device will be worn consecutively, except during water-based activities (i.e., taking a bath, swimming). Excluding attachment and removal days, the device will be worn for 24 h for seven consecutive days at four time points (baseline and 12, 24 and 36 months).

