### Sample size calculation

2.6

To detect a between-group difference over a 36-month period of 3 points on the RMDQ (i.e., the smallest worthwhile between-group difference that would justify the implementation of the intervention), with a standard deviation of 6 [49], a power of 85%, an alpha of 2.5%, a crossover rate of 15%, and allowing for a drop-out of up to 25%, a total of 318 patients are needed (i.e., 159 in each group) [50]. To detect a between-group difference of 15% over 36 months for the other co-primary outcome (physical activity), i.e., average number of steps with a standard deviation of 2448 steps [51], a power of 85%, an alpha of 2.5%, cross-over rate of 15%, and allowing for a drop-out of up to 25%, a total of 302 patients are needed. Therefore, 318 patients will be recruited.

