#### Primary and secondary outcomes

2.7.1

Linear mixed models with at least a two-level structure (i.e., time clustered within patients) will be used to analyse both co-primary outcomes; i.e., the difference in physical functioning and mean number of steps over a 7-day period during the 36-month treatment and follow-up period. The necessity of adding a third level (i.e., hospital) will be assessed using the −2 log-likelihood test. Time-by-group interaction terms will be used to detect differences between the groups at the various time points. Analyses will be adjusted for baseline confounders.

Secondary outcomes will be assessed using linear and logistic mixed models (depending on the nature of the dependent variable) using the same procedures as described above. Subgroup analyses will be performed to assess potential differences in outcome measures between people with different socio-economic status and the severity of LBP. Participants will be dichotomized into moderate or severe disability due to LBP based on a cut-off value of 40% on the RMDQ [52]. A RMDQ score of ≥40% (10 out of 24) indicates severe disability, while a score of <40% (9 out of 24) indicates moderate disability due to LBP. To test potential biases due to deviations from the intended intervention (e.g., crossovers), a per-protocol analysis will be performed in addition to the main intention-to-treat analysis.

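### Subgroup analysis is worded as a comparison of outcomes between kinds of patient, and severity is fixed as a two-way RMDQ split; a treatment interaction with continuous baseline RMDQ would be better

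*Protocol article*

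**What the plan says.** Three statements in section 2.7.1 (Primary and secondary outcomes) matter here.

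- The aim: "Subgroup analyses will be performed to assess potential differences in outcome measures between people with different socio-economic status and the severity of LBP".
- The severity split: "Participants will be dichotomized into moderate or severe disability due to LBP based on a cut-off value of 40% on the RMDQ". In points: "A RMDQ score of ≥40% (10 out of 24) indicates severe disability, while a score of <40% (9 out of 24) indicates moderate disability due" (the sentence ends by naming low back pain). The cut-off carries a reference. The text does not say at which visit severity is scored.
- The only interaction named: "Time-by-group interaction terms will be used to detect differences between the groups at the various time points". The groups there are the trial arms.

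Elsewhere, section 2.2 (Participants) requires "a physical functioning score of ≥4 out of 24 on the Roland-Morris Disability Questionnaire (RMDQ") at entry. Section 2.5.1 makes the RMDQ a co-primary outcome on which "scores can range from 0 (no disability) to 24 (severe disability"). No section gives the expected distribution of RMDQ at baseline.

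**The concern.** A subgroup analysis in a randomised trial should show whether the treatment effect differs between kinds of patient. The sentence describes something else: whether outcomes differ between kinds of patient. For severity the distinction is sharp, because the same questionnaire defines the strata and measures a co-primary outcome. Patients who start with high scores will tend to have higher scores later in either arm. A difference between strata found this way could be reported as evidence about who benefits when it shows only who started worse.

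The second issue is the cut. After the entry criterion the score can take 21 values (4 to 24). The severe stratum covers 15 of them (10 to 24) and the moderate stratum 6 (4 to 9). Scores of 9 and 10 are treated as different, and scores of 10 and 24 as the same. Where the treatment effect changes gradually with disability, an interaction test on the split has less power than one on the score itself.

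**Working it through.** **The plan's own figure.** The documents give no figure for the subgroup analysis, so the related one is the RMDQ sample size in section 2.6: difference 3, SD 6, power 85%, alpha 2.5% two-sided, crossover 15%, dropout 25%.

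- n per arm = 2 × [6 × (2.241 + 1.036) / 3]² = 85.95, so 86.
- Crossover: 86 / 0.85² = 119.03.
- Dropout: 119.03 / 0.75 = 158.7, so 159 per arm and 318 in total.

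This matches the stated 318. The sample size is not in question.

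**Cut-point.** 40% of 24 is 9.6, so 10 or more against 9 or less is consistent with the stated percentage.

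**Information kept by the cut.** For an interaction that is linear in RMDQ, the efficiency of the split relative to the continuous score is the squared correlation between the score and the indicator RMDQ ≥ 10:

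E = q(1 − q)(m1 − m0)² / v

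Here q is the share at 10 or more, m1 and m0 are the mean scores in the two strata, and v is the variance of the score. The baseline distribution is my assumption: a normal distribution discretised to whole points and restricted to 4-24, with location and SD stated before restriction.

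Example with location 12 and SD 5: q = 0.722, m1 = 14.45, m0 = 7.10, v = 4.42² = 19.5. Then E = 0.722 × 0.278 × 7.35² / 19.5 = 0.56.

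| Assumed location (SD 4 to 6) | Share severe | Gap between strata at entry, points | Information kept |
|---|---|---|---|
| 8 | 41-52% | 5.5-7.1 | 66-68% |
| 10 | 58-62% | 5.8-7.5 | 62-64% |
| 12 | 71-75% | 6.4-8.1 | 54-57% |
| 14 | 80-87% | 7.3-8.7 | 39-50% |
| 16 | 87-95% | 8.4-9.4 | 24-43% |

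A uniform distribution on 4-24 gives 71% severe and 61% kept. For reference, a median split of a normal variable keeps 2/π = 64%.

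The gap column bears on the literal reading. Under these assumptions the strata differ by 5.5 to 9.4 points before any treatment. The trial is designed around a treatment effect of 3 points ("To detect a between-group difference over a 36-month period of 3 points on the RMDQ").

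**Power.** Take an interaction that the continuous term would detect with 80% power at two-sided 5% (assumed). The power of the split is Φ[(1.960 + 0.842)√E − 1.960]:

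- E = 0.64: 61%
- E = 0.50: 51%
- E = 0.40: 43%

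**Detectable interaction with the split.** Assume 318 × 0.75 = 238 analysed, SD 6, two-sided 5% and 80% power, ignoring crossover and repeated measures. SE = √[4 × 36 / (238q) + 4 × 36 / (238(1 − q))], and the detectable difference in treatment effect is 2.802 × SE:

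- 50:50 split: SE 1.556, difference 4.4 points
- 70:30 split: SE 1.697, difference 4.8 points
- 80:20 split: SE 1.945, difference 5.4 points

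All three exceed the 3-point main effect.

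**The case against.** Four points can be made for the plan.

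- **Condensed wording.** In a two-arm superiority trial, subgroup analyses normally mean treatment effects across subgroups. The sentence follows one that carries over the procedures used for between-arm differences, and nothing says the arms will be pooled. A reader might infer that the sponsor has set out to answer the wrong question. The documents do not support that: one loosely worded sentence in a journal article does not establish intent, and an analysis plan that is not shown may name the interaction. What stands is that the stated contrast is not the one a subgroup analysis needs.
- **A prespecified, referenced cut.** Fixing it in advance prevents a data-driven choice, and the categories carry clinical labels. This is a good reason to keep the cut for presentation. It does not justify dropping the rest of the score when effect modification is tested. The point does not extend to socio-economic status, for which no cut is stated.
- **A possible threshold.** If the treatment effect really changes in a step at 10, the split is the efficient analysis and the linear term is the one that loses. This stands, and it limits the gain that can be claimed.
- **Limited consequence.** No power is claimed for subgroups, and a continuous term would not make the analysis confirmatory. This also stands.

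**Conclusion.** The point holds as a correction to a secondary analysis. Section 2.7.1 states a comparison of outcomes between kinds of patient, names no treatment-by-subgroup term, and fixes severity as a two-way split. Taken as written, the severity comparison would show a difference on RMDQ without any effect modification.

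If effect modification is intended, the split keeps roughly a quarter to two thirds of the information in the continuous score: 24-68% over the range assumed, and about 54-64% at location 10-12. A reader might infer a flat figure of about one half. The documents do not support it, because it needs a baseline RMDQ distribution that they do not give. In the range above, about one half corresponds to a mean baseline score near 13-14. All these figures also rest on a linear pattern of effect modification and on severity being scored at baseline, which the text implies but does not state.

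The co-primary analyses, their significance level and the sample size are unaffected.

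**What to change.** Reword the subgroup sentence in section 2.7.1 to say that the analysis tests whether the treatment effect differs by baseline RMDQ and by socio-economic status. In the planned mixed models, use a treatment-by-baseline-RMDQ interaction with RMDQ continuous, and a treatment-by-socio-economic-status interaction. State that severity is taken from the baseline score. Keep the referenced 10-point split for displaying treatment effects by category.

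The cost is wording only: the data and the models are those already planned. Recruitment runs to December 2026 with 36 months of follow-up, so the change can be made well before final outcomes exist. The downside is that a linear term is less efficient than the split if effect modification is truly a step at 10. Under either approach the subgroup analysis remains low-powered.

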#### Cost-effectiveness

2.7.2

The economic evaluation will be conducted in accordance with the Dutch Guideline for Economic Evaluations [53] and using the R codes developed by Jornada Ben et al. (2023) [54]. Analyses will be conducted from a societal and healthcare perspective for both the co-primary outcomes (i.e., physical functioning and physical activity) and QALYs. Cost and effect differences will be estimated simultaneously using a bivariate model, while accounting for the skewed nature of costs (using non-parametric bootstrapping), missing data (using MICE), baseline imbalances (using regression-based adjustment), and the clustered nature of data (using mixed models), if necessary [55]. Then, incremental cost-effectiveness ratios (ICER) will be calculated by dividing the difference in costs by the difference in effects. The uncertainty around the ICER and 95% confidence intervals surrounding the cost differences will be estimated by bias-corrected and accelerated bootstrapping analysis with 5.000 replications and graphically presented on cost-effectiveness planes [55]. Cost-effectiveness acceptability curves will be constructed, to assess the probability that the combined lifestyle intervention is cost-effective compared to usual care at different values of willingness to pay.

#### Process evaluation

2.7.3

The process evaluation follows a mixed method design [48]. Quantitative data obtained through the number of attended sessions, baseline and post-treatment questionnaires will be analysed using descriptive statistics.

The focus groups with participants and the semi-structured interviews with physio therapists will be analysed using thematic analysis [56]. First, concepts identified in the transcripts will be open coded. Similar concepts can receive the same code through axial coding. Thereafter, code patterns can be identified to create sub-themes, and will be discussed within the research group. Conceptually similar sub-themes can be grouped into overarching themes. Each theme will be analysed further and checked against all made codes and the dataset. Additional coding will be conducted if necessary. A second researcher will perform a concordance check on the final developed themes.

### Monitoring

2.8

Installing a data monitoring committee was not warranted due to the conservative and non-pharmacological nature of the intervention. Data monitoring will be done by an independent researcher once a year. All (Serious) Adverse Events reported by the participant or observed by the researcher will be recorded and reported. Serious Adverse Events will be reported to the Medical Research Ethics Committee (in Dutch: METC).

### Patient involvement

2.9

Patient representatives from the Dutch Association for Back Pain Patients (*Nederlandse Vereniging van Rugpatiënten ‘de Wervelkolom’*) and the Dutch Association for Overweight and Obesity (*Nederlandse Vereniging voor Overgewicht en Obesitas*) are members of the study consortium. They were actively involved in the design phase of the trial to help ensure that the intervention and research procedures are aligned with the needs and perspectives of the target population. Their involvement extends throughout the study, including advising on patient engagement strategies during recruitment, contributing to the development of accessible study materials, and supporting the dissemination of results to broader patient communities.

### Data management

2.10

A data management plan has been developed to ensure that data handling aligns with FAIR (Findable, Accessible, Interoperable and Reusable) principles. At baseline, each participant will be assigned a unique, computer-generated identification code that bears no relation to personal data. All collected data will be pseudonymised using this code. Data include signed informed consent forms, questionnaires and physical measurement reports. These will be stored in CastorEDC, a secure data management system (Castor Electronic Data Capture. https://castoredc.com). Baseline and follow-up data will be entered into this system, and data obtained from the ActivPAL will be exported directly to a secure research drive accessible only to the research team at Vrije Universiteit Amsterdam. To ensure data quality, the online questionnaires include pre-programmed data constraints, and frequent consistency checks are performed.

### Ethics and dissemination

2.11

The study protocol was approved by a medical ethics committee (METC Brabant: NL85373.028.23) and has been registered at ClinicalTrials.gov (NCT06594796). Important protocol modifications will be approved by the METC before implementation. All participants will provide informed consent before trial inclusion. Participants retain the right to request for deletion of their data. Study data will be archived for 15 years after study inclusion. Trial datasets will be made available upon reasonable request.

Results of the study will be published in peer-reviewed scientific journals and presented at (inter)national conferences. At the end of the study, participants will receive their own data regarding their health outcomes upon request.

## Discussion

3

This paper describes the protocol of the Back2Health study, which is designed to investigate the (cost-)effectiveness of a combined lifestyle intervention integrated with standard care for LBP according to national guidelines for patients with persistent non-specific LBP who are overweight or obese and referred back from secondary care to primary care.

This is the first RCT to integrate a lifestyle intervention into clinical care for LBP. A systematic review including three RCTs evaluating lifestyle interventions for LBP showed only modest results regarding the clinical effectiveness of a lifestyle intervention in reducing LBP outcomes [28]. However, the interventions that were studied varied highly in dosage (i.e., number of sessions and duration of intervention), content (training program or telephone-based coaching), professionals involved (i.e,. mono or multidisciplinary) and country of implementation. In addition, these interventions were generally of shorter duration and focused on a limited number of lifestyle factors. In contrast, the current intervention evaluates a two-year multidisciplinary, personalised lifestyle programme integrated into standard LBP care, targeting multiple lifestyle domains (physical activity, diet, sleep, and stress) using behaviour change techniques."

Previous studies on the effectiveness of the combined lifestyle intervention have demonstrated its effectiveness in supporting adults in adopting more sustainable behaviours, leading to weight reduction and improvements in lifestyle factors, such as diet and physical activity [21,22]. However, while excess weight is a known prognostic factor for LBP, prior research also suggests that differences in physical functioning and physical activity levels significantly impact the quality of life in this patient population [3]. Therefore, both outcomes have been selected as co-primary outcomes to examine the effects of the intervention in overweight and obese LBP patients.

A major strength is that the intervention builds on the existing combined lifestyle interventions and other existing interventions recommended in national guidelines, which increases the chance of successful implementation when the intervention is deemed (cost-)effective. However, since the combined lifestyle intervention is not currently tailored to our patient group (i.e., people with persistent LBP), a process evaluation is needed to gain insight into the implementation and usefulness of its various components. In addition, the inclusion of multiple distinct combined lifestyle intervention programs to better reflect routine clinical practice may lead to variability within the experimental intervention arm, potentially introducing heterogeneity in the outcomes. Furthermore, the control arm receives usual care without restrictions, aside from being asked to not participate in combined lifestyle interventions. Consequently, control participants may still engage in lifestyle modifications independently, including consulting health professionals such as dieticians or personal trainers. This may attenuate the observed differences between the intervention and control arm. In response, healthcare usage (e.g., medical, allied health, medication and other) will be systematically recorded in both study arms.

A potential limitation could be that participants may perceive the 36-month duration of the trial as too long. To mitigate this, questionnaires and measurements have been carefully selected to minimize participant burden. Additionally, to maintain engagement throughout the study, participants will receive postcards on special occasions (e.g., birthdays and holidays) and periodic updates.

In summary, the Back2Health trial will provide much needed insight in the (cost-)effectiveness of a comprehensive, personalised treatment integrating lifestyle and clinical factors) for people with chronic non-specific LBP who are also overweight or obese, compared to a usual care approach. The trial will evaluate its impact on clinical outcomes, including self-reported physical functioning and objectively measured physical activity. Integrating lifestyle into the treatment of low back pain may also provide an opportunity to address lifestyle-related comorbidities that co-occur in this population, contributing to broader improvements in health and wellbeing.

## Data Availability

No data was used for the research described in the article.
